#### Recruitment and sampling

We will approach all women with sFGR as defined by the eligibility criteria. Further to two no-cost extensions granted by the NIHR due to delayed setup and recruitment and rarity of the condition under study, there will be a 42-month data collection period (39-month recruitment) from 22 UK sites, (compared with the originally proposed 18-month data collection period). The planned start and end dates for the study are 1 July 2021 and 30 November 2025, respectively. Our recent survey suggests that we should be able to recruit two women per month per centre; if we assume a conservative 40% recruitment rate, our pragmatic estimate is that we will recruit over 100 women in the study period. All participants will be recruited from their local fetal medicine or antenatal clinic. They will be contacted in person by a member of the clinical research team (principal investigator (PI)/research midwife/delegated authority) and invited to take part in the study. Potential participants will be given written and verbal information on the FERN study and provided with the opportunity to ask questions and take any additional time required to consider taking part in the study. Following this, participants will be asked to sign the study-specific informed consent form in the presence of the site researcher. Once eligibility has been confirmed by the PI at the site, and informed consent has been obtained, the participant will be registered and then entered into the study using a bespoke electronic data capture system that will generate a unique participant identification number. The data will be collected on a range of data items described on the FERN REDCap database. The follow-up will continue until of discharge of baby/babies from the hospital/neonatal unit. This database is designed and maintained by the University of Liverpool, IT Services in collaboration with the chief investigator and research manager. The eCRF (electronic case record form) is the primary data collection instrument for the study. All data requested on the eCRF must be recorded and all missing data explained. WP1 is a prospective observational study, therefore, all data will be collected prospectively by trained members of the research team at each study site.

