### Sample size calculation

No formal power calculation or primary outcome data will be determined for any WP in this study as this is a feasibility study and does not involve any formal hypothesis testing. We will assess the feasibility of recruiting women with an MC twin pregnancy complicated by sFGR to collect detailed information about pregnancy management and outcomes. The success of this WP will be determined by the acceptability of the study by women and clinicians. This will be determined as the ability to recruit and retain participants. We would expect to recruit in the region of 100 participants across the UK over a 39-month period, but we will continue to recruit until the recruitment period is complete. This is a pragmatic number which is based on the typical number of sFGR patients seen per annum in large consultant-led NHS units within the UK.

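### The stated recruitment inputs for WP1 multiply to about 686 women, not the roughly 100 that the protocol projects

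*Protocol article*

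**What the plan says.** The WP1 section on recruitment and sampling sets the scale of the study: "there will be a 42-month data collection period (39-month recruitment) from 22 UK sites". It explains that two extensions were granted because of delayed setup and recruitment and the rarity of the condition, and gives the contrast "compared with the originally proposed 18-month data collection period". It then takes a rate from a survey and applies an uptake, "we should be able to recruit two women per month per centre; if we assume a conservative 40% recruitment rate", and concludes "our pragmatic estimate is that we will recruit over 100 women in the study period".

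The section on sample size calculation restates the expectation: "We would expect to recruit in the region of 100 participants across the UK over a 39-month period". It describes the number as pragmatic and gives it another basis, "based on the typical number of sFGR patients seen per annum in large consultant-led NHS units within the UK", without a caseload figure. The abstract also gives 100 pregnancies as the pragmatic sample size for WP1.

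**The concern.** A projection should follow from the inputs printed beside it, and this one does not. In many protocols a loose accrual sentence would hardly matter. Here recruitability is what the study investigates. The sample size section defines WP1's success through the ability to recruit and retain participants, the primary objective names numbers of cases among its elements, and this projection is the only numeric recruitment benchmark for WP1 in the document.

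As written, the benchmark has two very different values. A final count near 100 would meet the expectation in words while falling far below what the stated inputs predict. A reader planning the later trial could not tell which accrual rate the investigators had expected.

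**Working it through.** **Inputs, all from the WP1 section on recruitment and sampling**

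- Sites: 22
- Recruitment months: 39 (data collection: 42)
- Women per centre per month, from the survey: 2
- Recruitment rate: 40%

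**Attempt to reproduce the stated figure**

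Expected recruits = sites × months × rate × uptake
= 22 × 39 × 2 × 0.40 = 858 × 0.80 = 686.4

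The stated figure is about 100, so it is not reproduced: 686.4 / 100 = 6.9. Conversely, 100 / 686.4 = 14.6%.

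**Other readings**

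| Reading | Calculation | Women |
|---|---|---|
| 40% not applied | 22 × 39 × 2 | 1,716 |
| 42 months instead of 39 | 22 × 42 × 0.80 | 739 |
| Sites open linearly over 39 months | 686.4 / 2 | 343 |
| Original 18 months, 22 sites | 22 × 18 × 0.80 | 317 |
| 15 months (18 less the present 3-month gap), 22 sites | 22 × 15 × 0.80 | 264 |
| 18 months, linear opening, 22 sites | 316.8 / 2 | 158 |
| Two per month across the whole study, 39 months | 2 × 39; then × 0.40 | 78; 31 |
| Two per year per centre | 2 × 22 × 39/12; then × 0.40 | 143; 57 |

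None gives about 100.

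**How far one input would have to move to give 100, the others held fixed**

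- Site-months: 100 / 0.80 = 125, against 22 × 39 = 858. That is an average of 125 / 22 = 5.7 open months per site, or 125 / 39 = 3.2 sites open throughout.
- Uptake: 100 / 1,716 = 5.8%, against 40%.
- Survey rate: 100 / (858 × 0.40) = 0.29 women per centre-month, against 2.

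These are three alternative ways to close the same gap. They are not estimates, and a mixture of smaller changes would also close it.

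**The case against.** The strongest defence is that the sentence is simply out of date. The original plan had 18 months of data collection, and its number of sites is not stated. Seven sites would give 7 × 18 × 0.80 = 100.8. That may be what happened, but seven sites appear nowhere in the document, and the sentence now stands beside 22 sites and 39 months. A stale sentence would explain the mismatch; it would still need correcting.

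A second defence is that 686 does literally exceed 100. That would carry weight if the figure were only a lower bound, but the sample size section and the abstract both treat 100 as the expected size.

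Third, nothing in the analysis depends on the projection. There is no power calculation, recruitment runs to the end of its period whatever the count, and no pass mark is set at 100. This stands: no estimate, interval or stopping decision changes.

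Stronger conclusions are tempting but unsupported:

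- A reader might infer that the survey's case rate is wrong about sevenfold. The factor of 6.9 belongs to the product of all the inputs. It equals the case-rate error only if uptake is exact and all 22 sites were open for the full 39 months. The document does not say so, and it reports delayed setup.
- A reader might test the rate against the introduction's figure that sFGR affects 10–15% of monochorionic twin pregnancies. Two per month is 24 per year, which would need 24/0.15 = 160 to 24/0.10 = 240 such pregnancies per site-year. Centres that receive referrals may see a higher proportion, and no catchment data are given, so this settles nothing.
- A reader might infer that the feasibility verdict, or WP3's power and economic work, rests on the survey rate. The document says that WP3 uses the information from WP1 and WP2, and that preferences, equipoise and current practice also count.
- The two bases for the 100 differ, but the annual-caseload basis has no figure, so they cannot be shown to conflict numerically.

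**Conclusion.** The point holds as an error in the stated projection. Taken as printed, with all 22 sites recruiting for 39 months, the inputs imply about 686 women, 6.9 times the expected 100 or so. Uneven site opening alone would have to be extreme to explain this, leaving about 15% of the nominal site-months. At least one of survey rate, uptake and open site-months is therefore wrong or outdated, and the document does not allow the gap to be attributed to any one of them.

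The consequence is for how recruitment success is read, not for any statistical result: 100 women would be all of the stated expectation but about 15% of what the inputs predict. In a study whose question includes whether enough women can be recruited, that should be corrected before the results are interpreted.

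**What to change.** Choose one of two restatements in the WP1 section on recruitment and sampling:

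1. Give the current eligible rate per site, the uptake and the actual open site-months, each with its source, so that their product reproduces the stated target. The inputs should come from site data. Rates solved backwards from 100 would only hide the mismatch.
2. Keep the present inputs, state the expectation as about 686, and report the shortfall against it as a feasibility result.

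In either case, reconcile the projection with the annual-caseload basis in the section on sample size calculation, so that 100 has one traceable origin. Report observed eligible women and recruited women per open site-month, each with a 95% CI, and name these as the accrual input to WP3.

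The cost is a few sentences of protocol wording, one extra descriptive rate (which needs site opening dates and a count of eligible women), and a stated accrual expectation that looks less favourable.

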### Sample size calculation

No formal power calculation or primary outcome data will be determined for any WP in this study as this is a feasibility study and does not involve any formal hypothesis testing. We will assess the feasibility of recruiting women with an MC twin pregnancy complicated by sFGR to collect detailed information about pregnancy management and outcomes. The success of this WP will be determined by the acceptability of the study by women and clinicians. This will be determined as the ability to recruit and retain participants. We would expect to recruit in the region of 100 participants across the UK over a 39-month period, but we will continue to recruit until the recruitment period is complete. This is a pragmatic number which is based on the typical number of sFGR patients seen per annum in large consultant-led NHS units within the UK.

### Patient and public involvement

No patient and public involvement was sought during the set up or design of this feasibility study.

### Outcome measures

This study will assess the feasibility of collecting outcome data from women with an MCDA twin pregnancy complicated by sFGR.

### WP 2: exploring patients’ and clinicians’ views

This will involve qualitative research, including interviews and focus groups (if there is divergence of opinion about trial acceptability) with women and their partners (if applicable), as well as with clinicians involved in the management of MC twin pregnancies. Qualitative methods will explore parents’ and clinicians’ perspectives on:

Future trial design including views on active intervention and expectant management, randomisation, outcomes, and approach to recruitment and consent, including decision-making and length and content of trial information materials.Factors influencing parent and clinician decision-making when potential outcomes include death or serious disability of one or both twins.Acceptability of a future trial, including potential barriers to recruitment, consent decisions, trial procedures, equipoise; inclusion/exclusion criteria and training needs.

#### Eligibility criteria

Mothers and partners (if applicable) of MCDA twin pregnancies complicated by sFGR in the previous 3 years; and clinical staff involved in the management of MC twin pregnancies.

#### Recruitment and sampling

Women and their partners (if applicable) will be recruited through two routes to maximise the potential participation within the recruitment period and ensure that women from all management groups are represented. First, all women and partners (if applicable) approached to take part in WP1 will be invited to consent to be contacted by a member of the WP2 research team to discuss taking part in this aspect of the study, regardless of ultimate participation in WP1. Second, the qualitative research team will contact stakeholders (eg, charity leads/chief executive officers) of twin support groups (eg, Ttwins Trust—formerly Twins and Multiple Births Association) inviting them to post a FERN study media advert on the support group’s website and/or social media pages (eg, Facebook and Twitter) or member email lists. If divergence in opinions on trial intervention and acceptable outcomes is observed in the early analysis of interviews, we will use social media (route 2) to recruit parents to a focus group (~6–10 parents) in the Northwest of England (pragmatic choice as location of the qualitative study team) with the aim of reaching a consensus about an acceptable trial design. A focus group topic guide will be developed based on interview findings.

For clinician recruitment, a comprehensive database of clinicians, nationally and internationally, who lead the management of sFGR will be developed by the CI, coapplicant team and collaborators. This database will be used to identify which clinicians will be invited to take part in this aspect of the study. Second, an FERN practitioner online recruitment advert will be posted on relevant social media pages. As with the women and partner interviews, if divergence in opinions is observed in the early analysis of interviews, clinicians will be recruited to a focus group (~8–10 site healthcare professionals) with the aim of reaching consensus about an acceptable trial design. A focus group topic guide will be developed based on interview findings.

#### Sample size calculation

To ensure sample variance, we will include parents with experience of intervention and expectant management of sFGR, bereaved and non-bereaved parents, and clinicians in favour of both fetal intervention and expectant management. Interviews will be conducted till we achieve information power,^21^ which is the point at which data addresses the study aims; sample variance (eg, parents offered expectant management or intervention, bereaved and non-bereaved parents, and clinicians in favour of intervention or expectant management) and, use of theory (eg, bioethical principles) and quality of dialogue.

#### Primary outcome measures

Qualitative element of the study will explore parents’ and clinicians’ perspectives and present a summary of findings and recommendations about trial design/feasibility to feed into WP3.

### WP 3: consensus development to determine feasibility of a trial

We will use the information provided in WP1 and WP2 to develop a consensus on a future definitive study. The effect of a design of a future RCT, if deemed acceptable and feasible, on management of sFGR in MC twin pregnancy will be assessed: power calculation, economic feasibility, identifying the research cohort (involving subtypes, gestation, intervention and control arms) and key outcomes.

A survey of clinicians will be performed as part of WP3 to identify current practices and opinion. Clinicians from the curated database of experts will be invited to participate in the survey. The results of this survey will be used to inform the selected consensus process approach that will ultimately formulate optimal trial design for use in a planned clinical trial in women with MC twin pregnancies complicated by sFGR. Depending on the results and findings of the previous WPs, we will take an adaptive approach when it comes to reaching a consensus on determining whether a future trial is possible (eg, this could take the form of a Delphi survey or a structured consensus meeting). Important issues and trial design constructs raised from these previous work streams will be formulated into a series of structured items for consideration. We will aim for at least 50% or more voting on the feasibility and acceptability of the study design/eligibility to take things forward as ‘plausible’. Plausibility will be defined as items where at least 50% of the voting participants deem the item as feasible and acceptable. An iterative process will be followed to allow further discussion on items when needed. The consensus opinion of relevant stakeholders on key preferred scenarios will be used to develop a protocol for this planned trial. The feasibility of this protocol will then be further consolidated using qualitative research and a final consensus process. If it becomes apparent that an RCT would not be feasible/acceptable, future research design would be agreed on by a structured consensus meeting.

### Statistical/data analysis considerations

Patients will be analysed on an intention-to-treat basis at the time of recruitment, retaining all patients irrespective of any protocol deviations. Further secondary analysis will be carried out on a per-protocol population. Further analyses may be carried out on planned subgroups (eg, those who meet the inclusion criteria for a future study) as required. As this is an exploratory study no formal levels of significance are set. All statistics will be presented alongside 95% CIs to give an indication of the level of precision. The likelihood of missing data is small given the standard procedure in place to manage the study centrally. Final analyses will take place on a complete-case basis with no adjustments made (eg, multiple imputation) in the case of missing data. Analysis of study data will take place once all participants have received the planned follow-up and all data are available for analysis. Continuous data will be summarised as median, IQR and ranges. Categorical data shall be summarised as frequencies of counts and associated percentages. Multivariate data analysis techniques will be used to attempt to find natural groupings in the generated data. In particular, hierarchical cluster analysis and principal component analysis techniques will be used.

Thematic analysis of qualitative data from the WP2 interviews and focus group(s) will be assisted by using NVivo V.12 qualitative data analysis package and SPSS, version 27 software for statistical analysis. While data will be analysed thematically, the focus will be modified to fit with the criterion of catalytic validity, whereby findings should be relevant to future research and practice (in particular, the design of the potential definitive RCT). Analysis will also draw on philosophical theory, concepts and methods (such as conceptual clarification and balanced argumentation) in an aim to develop recommendations that are defensible and consistent with key principles of biomedical ethics. This empirical ethics approach will facilitate the identification of practices or processes that should be challenged or modified in trial design. Quantitative analysis will involve simple descriptive statistics and the χ^2^ test for trends. Data from each method will be analysed separately then synthesised using constant comparative analysis. If it becomes apparent that an RCT would not be feasible/acceptable, future research design would be agreed on by a structured consensus meeting.

### Data monitoring

As there are no formal hypotheses being tested, there are no formal stopping rules (other than safety) or mechanisms defined here to stop the study prior to the planned end of the study. The study does have a formal independent oversight committee that will be able to review at regular intervals all accumulating data. The main responsibility of this committee will be to review the recruitment of participants, the collection of all essential data and to assess patient safety. The study oversight/steering committee will consist of (1) chief investigator, (2) independent clinician (chair), (3) research manager, (4) study statistician, (5) another independent clinician; (6) (patient and public involvement and engagement) coapplicant, (7) sponsor and (8) lead site representative. The role of the oversight/steering committee is to provide oversight of the study. In particular, this committee will concentrate on the progress of the study, adherence to the protocol, participant safety and consideration of new information.

### Ethics and dissemination

This study has received ethical approval from the Health Research Authority (HRA) Ethics Committee South West—Cornwall and Plymouth (REC reference 20/SW/0156, IRAS ID 286337), but all participating sites must undergo site-specific assessment of capacity and capability via the HRA. Any adverse events or protocol deviation will be identified and reported. The study will be conducted in accordance with, but not limited to, the Human Rights Act 1998, the Data Protection Act 2018, Freedom of Information Act 2000 subject to the provisions of sections 41 and 43 thereof, the EU (European Union) Clinical Trials Directive, ICH-GCP (International Council for Harmonisation Guideline for Good Clinical Practice), the Declaration of Helsinki 1996 and the UK Policy framework for Health and Social Care research as amended from time to time. All data will be recorded, collected, stored and processed, in accordance with GDPR(General Data Protection Regulation) (EU) 2016/679.
